## Abstract

**Background:**

Scarce information exists regarding the preventive effect of periodontal treatment in the recurrence of cardiovascular events. Prevention may be achieved by targeting risk factors for recurrent coronary artery disease (CAD) in patients with previous history of cardiovascular events. The aim of this trial is to compare the effect of two periodontal treatment approaches on levels of C-reactive protein, lipids, flow-mediated dilation and serum concentrations of proinflammatory and endothelial markers in stable CAD patients with periodontitis over a period of 12 months.

**Methods/design:**

This is a randomized, parallel design, examiner blinded, controlled clinical trial. Individuals from both genders, 35 years of age and older, with concomitant diagnosis of CAD and periodontitis will be included. CAD will be defined as the occurrence of at least one of the following events 6 months prior to entering the trial: documented history of myocardial infarction; surgical or percutaneous myocardial revascularization and lesion >50% in at least one coronary artery assessed by angiography; presence of angina and positive noninvasive testing of ischemia. Diagnosis of periodontitis will be defined using the CDC-AAP case definition (≥2 interproximal sites with clinical attachment loss ≥6 mm and ≥1 interproximal site with probing depth ≥5 mm). Individuals will have to present at least ten teeth present to be included. One hundred individuals will be allocated to test (intensive periodontal treatment comprised by scaling and root planing) or control (community periodontal treatment consisting of one session of supragingival plaque removal only) treatment groups. Full-mouth six sites per tooth periodontal examinations and subgingival biofilm samples will be conducted at baseline, 3, 6 and 12 months after treatment. The primary outcome of this study will be C-reactive protein changes over time. Secondary outcomes include levels of total cholesterol, LDL-C, HDL-C, triglycerides, IL-1β, IL-6, TNFα, fibrinogen, ICAM-1, VCAM-1 and E-selectin. These outcomes will be assessed at all time points over 12 months. Flow-mediated dilation will be assessed at baseline, 1, 3 and 6 months after periodontal therapy.

**Discussion:**

This trial will provide new evidence regarding the effect of periodontal treatment on risk markers for recurrence of cardiovascular events in stable coronary artery disease patients.

**Trial registration number:**

ClinicalTrials.gov Identifier, NCT01609725

## Background

Cardiovascular diseases (CVD) are still considered the main cause of mortality and morbidity all over the world [1]. In the last years, efforts have been made to define the inflammatory pathways that lead to cardiovascular events aiming to define more effective therapeutic and preventive strategies. In this regard, it has been demonstrated that many proinflammatory biomarkers play an important role in the cascade of events observed in CVD, mainly C-reactive protein (CRP) and other molecules such interleukins, fibrinogen and adhesion molecules [2-4].

Periodontal diseases have been considered a probable risk factor for CVD with a great amount of evidence from observational studies associating the two conditions [5-10]. The increase in the risk of coronary artery disease in periodontal patients is estimated to be 24% higher after adjusting for important confounding factors [11]. Despite the considerable amount of evidence associating the two conditions, there is still lack of interventional studies to better elucidate the effect of periodontal treatment on the prevention of CVD [10,12].

The biological plausibility linking periodontal diseases to CVD is supported by the findings that periodontal inflammation and infection lead to an increase in blood levels of the above-mentioned important biomarkers related to CVD. For instance, levels of CRP are higher in periodontitis compared to healthy patients, and reduction of this marker is observed after periodontal therapy in otherwise healthy individuals [13,14]. Interleukin 1β, interleukin 6, fibrinogen and other proinflammatory biomarkers have also been found in elevated levels in healthy patients with periodontitis [15,16]. It has also been demonstrated that periodontal disease may negatively influence endothelial function directly or indirectly [17-20].

Although there are some interventional studies evaluating the systemic effects of periodontal therapy [14], there is little information regarding the impact of periodontal treatment on the recurrence of cardiovascular events. Most of the studies have been conducted with otherwise healthy patients with periodontitis, limiting the applicability of the findings to patients suffering from CVD. To the best of our knowledge, there are no randomized controlled trials published to date assessing the preventive effect of periodontal therapy in true endpoints of cardiovascular disease, i.e., major cardiovascular events such as myocardial infarction and stroke. By reviewing the literature, we were able to find two small interventional studies showing that periodontal treatment might reduce some CVD blood risk markers. One of the studies demonstrated that CRP and hemostatic factors improved after periodontal treatment in a small group of 18 non-smokers with a history of a recent CVD event [21]. Another study evaluated hypertensive patients with periodontitis and showed that periodontal therapy might reduce levels of CRP and fibrinogen [22].

Recently, a study protocol of a short-term randomized controlled trial about the effect of periodontal therapy on endothelial function and some blood biomarkers for CVD was published [23]. The study is planned to be conducted with systemically healthy individuals with periodontitis and will provide data for primary prevention of CVD.

The aim of this article is to describe the protocol of a randomized controlled trial that was designed to compare the effect of intensive and community periodontal treatments on levels of C-reactive protein, lipids, flow-mediated dilation and serum concentrations of proinflammatory and endothelial markers in stable coronary artery disease patients with periodontitis over a 12-month period.

## Methods/design

### Study design and centers

This is a randomized, parallel design, examiner-blinded, controlled clinical trial. This study will be conducted at the School of Dentistry of the Federal University of Rio Grande do Sul and at the University Hospital of Porto Alegre in Brazil. Cardiovascular patients will be recruited at the Ischemic Heart Disease Clinic at the university hospital. Blood samples and laboratory analyses will be conducted at the Clinical Research Center at the university hospital. Flow-mediated dilation will be performed at the sector of non-invasive methods of the university hospital. Periodontal clinical examinations and treatments will be conducted at the Periodontal Department of the School of Dentistry.

### Inclusion and exclusion criteria

Individuals from both genders, 35 years of age and older, with concomitant diagnosis of CAD and periodontitis will be selected for the study. The diagnosis of CAD will be recalled from the history of acute coronary syndrome episodes or percutaneous/surgical revascularization [24] recorded at the hospital files. Specifically, CAD will be defined as the occurrence of at least one of the following events 6 months prior to entering the trial: documented history of myocardial infarction; surgical or percutaneous myocardial revascularization and lesion >50% in at least one coronary artery assessed by angiography; presence of angina and positive noninvasive testing of ischemia.

Diagnosis of periodontitis will be defined using the CDC-AAP case definition [25]. Individuals will be classified as having severe chronic periodontitis in the presence of ≥2 interproximal sites with clinical attachment loss ≥6 mm and ≥1 interproximal site with probing depth ≥5 mm in non-adjacent teeth. Moreover, included individuals have to present at least 12 teeth.

Individuals will be excluded from the study if they use antibiotics or anti-inflammatory drugs during the follow-up period of the study.

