### Cardiovascular care

This study will be conducted with stable coronary artery disease patients who will be receiving cardiovascular care for at least 6 months at the Ischemic Heart Disease Clinic, a tertiary care cardiovascular clinic, at the University Hospital of Porto Alegre. Cardiovascular care provided in this tertiary clinic includes medication and counseling. The staff of the clinic comprises cardiologists, nurses, nutritionists and physiotherapists. The protocol of cardiovascular care in this clinic includes statins for the majority of the patients. When appropriate, oral hypoglycemic, insulin, acetylsalicylic acid and antihypertensive drugs are also prescribed. Counseling includes mainly health-related lifestyle behavioral modifications such as daily exercise, smoking cessation and dietary therapy. The mean follow-up time of the patients that attend the clinic is 5 years.

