### Interventions

The test group (TG) will consist of intensive periodontal treatment comprising one session of supragingival scaling and personalized oral hygiene instructions, followed by one to four sessions of subgingival scaling and root planing (SRP) by quadrant, under local anesthesia, in a period of 14 days. Individuals will be followed monthly during the first 6 months and at each 3 months until the end of the 12-month study period. In the follow-up sessions, professional plaque removal, oral hygiene instructions and reinforcement will be provided.

The control group (CG) will receive community periodontal treatment similar to that provided by the Brazilian public health system, consisting of only one session of supragingival scaling followed by standard oral hygiene instructions.

Treatments will be performed by two experienced periodontists ([name] and [name]). Before the beginning of the study, the two clinicians will undergo a period of training and discussion of the therapeutic approaches with the aim of standardization of the test and control interventions.

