**Figure 1 F1:**
[figure not shown]
Flowchart of the study participation and examinations.

•Visit I: application of a structured questionnaire, general clinical evaluation, baseline periodontal examination and subgingival microbiological samples.

•Visit II: baseline flow-mediated dilation, anthropometric assessment and blood samples.

•Visit III: Start of periodontal treatment according to randomization. After this visit, periodontal therapy will be conducted according to randomization.

•Visit IV (30 days after the last session of periodontal treatment): first follow-up flow-mediated dilation assessment.

•Visit V (3 months after the last session of periodontal treatment): second follow-up flow-mediated dilation assessment, first follow-up blood samples, periodontal clinical examination and subgingival microbiological samples.

•Visit VI (6 months after the last session of periodontal treatment): third follow-up flow-mediated dilation assessment, second follow-up blood samples and periodontal clinical examination and subgingival microbiological samples.

•Visit VII (12 months after the last session of periodontal treatment): final follow-up blood samples, periodontal clinical examination and subgingival microbiological samples.

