### Demographics, behavioral and clinical variables

A structured questionnaire will be applied to all participants to obtain demographic and behavioral data. Age, socioeconomic level, education, medication use, smoking habits and frequency of physical activities will be recorded. Individuals will be examined clinically to measure height, weight and blood pressure. Body mass index (BMI) will be calculated dividing the weight by the square of the height.

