### Primary outcome

The primary outcome of the present trial will be changes in serum concentrations of C-reactive protein.

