### Statistical analyses

Continuous variables will be described using means and standard deviations or median and range in case of asymmetric distribution of data. Categorical variables will be presented using frequency distribution. An intention-to-treat approach will be used in the analysis of this trial taking into consideration all dropouts during the follow-up period.

Univariate analyses will be conducted using chi-square and *t* tests for independent samples. Multivariate models will be fitted using generalized estimating equations to compare changes in each outcome according to test and control periodontal treatment groups controlling for confounding factors. *P* values <0.05 will be considered statistically significant. A statistical package (Stata 12 for Macintosh, STATA Corp., College Station, TX, USA) will be used. The individual will be considered the unit of analysis.

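### Removing randomised patients for antibiotic or anti-inflammatory use during follow-up conflicts with the intention-to-treat analysis and creates missing CRP data related to the outcome

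*Protocol article*

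**What the plan says.** All references are to the protocol article.

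- **Inclusion and exclusion criteria:** "Individuals will be excluded from the study if they use antibiotics or anti-inflammatory drugs during the follow-up period of the study". No drug list, dose, duration or exception is given.
- **Visit list under Figure 1:** "Visit III: Start of periodontal treatment according to randomization". Visits IV to VII follow at 1, 3, 6 and 12 months after the last treatment session.
- **Statistical analyses:** "An intention-to-treat approach will be used in the analysis of this trial taking into consideration all dropouts during the follow-up period". The comparison uses generalized estimating equations (GEE).
- **Primary outcome:** "The primary outcome of the present trial will be changes in serum concentrations of C-reactive protein".
- **Interventions**, for the test group: "Individuals will be followed monthly during the first 6 months and at each 3 months until the end of the 12-month study period". The control group has a single treatment session.
- **Study design and centers** and **Cardiovascular care:** patients come from the Ischemic Heart Disease Clinic, of which the article says "When appropriate, oral hypoglycemic, insulin, acetylsalicylic acid and antihypertensive drugs are also prescribed".
- **Demographics, behavioral and clinical variables:** "Age, socioeconomic level, education, medication use, smoking habits and frequency of physical activities will be recorded". In the visit list the questionnaire appears at Visit I only.

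**The concern.** An exclusion criterion normally acts before allocation. This one depends on what happens to a patient over the following 12 months. It therefore takes out randomised patients because of a later event, and that event bears on the outcome: an infection or inflammatory episode that leads to these drugs can also move CRP and the inflammatory secondary outcomes (IL-1β, IL-6, TNFα, fibrinogen).

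The event may also depend on arm. The two treatments differ in intensity, and staff meet test patients more often, so drug use could come to light more readily there even if true use is equal. Blinding is described for the examiner and the statistician, not for the treating periodontists.

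At stake is the comparability of the arms for the primary outcome. A larger sample would not restore it, and samples not taken cannot be recovered later.

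**Working it through.** **1. Timing.** Treatment by allocation starts at Visit III, and every follow-up visit comes later. A rule triggered during follow-up can therefore apply only to randomised patients. No section says that those excluded remain under observation, remain in the analysis, or count as dropouts.

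**2. Contacts.** In the test arm, maintenance sessions at months 1 to 6 (6), 9 and 12 (2) make 8. Assessment visits IV to VII make 4 in both arms. Some test-arm contacts may fall on the same day, but controls have only the 4 assessments after their one treatment session. The article does not say at which contacts drug use is ascertained, so unequal detection is possible but not established.

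**3. Planned effect.** Sample size section: reductions of 1.5 mg/l (SD 1.5) and 0.5 mg/l (SD 0.5), so the planned difference is 1.5 − 0.5 = 1.0 mg/l.

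**4. Shift from unequal removal.** Let m be an arm's mean reduction with everyone followed, q the share removed, and d the amount by which the reduction in those removed is smaller than in those retained. If r is the mean of those retained, m = (1 − q)r + q(r − d) = r − qd, so r = m + qd. The values of q and d are assumptions; the article gives none.

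| Removed, test / control | d (mg/l) | Test mean | Control mean | Difference | Shift |
|---|---|---|---|---|---|
| 10% / 10% | 1 | 1.60 | 0.60 | 1.00 | 0 |
| 10% / 20% | 1 | 1.60 | 0.70 | 0.90 | −0.10 |
| 20% / 10% | 1 | 1.70 | 0.60 | 1.10 | +0.10 |

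Consistency with the plan: a 20/80 split with gap d contributes an SD of √(0.2 × 0.8) × d. For d = 1 this is 0.4 mg/l, within the planned control SD of 0.5. For d = 2 it is 0.8 mg/l, which exceeds it. A control-arm gap of 2 mg/l, and the 0.2 mg/l shift it would give, is therefore incompatible with the protocol's own planning values.

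**5. A second model.** Simulation assuming no true effect, SD 1.118 in both arms, and odds of removal rising with CRP change (log-odds 1 per SD). Removal of 10% in each arm gives a bias of about 0. Removal of 5% test and 20% control gives about 0.14 mg/l against the test arm, and the reverse gives about 0.14 mg/l in its favour. Removal of 10% test and 30% control gives about 0.18 mg/l against the test arm. The common SD is larger than the plan's control SD, so these are illustrations only.

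**6. Scale.** With 50 × 0.8 = 40 per arm, the standard error of the difference is √((1.5² + 0.5²)/40) = 0.25 mg/l. A shift of 0.10 is 0.4 of a standard error.

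**7. Numbers and power.** The stated 42 per arm is not reproduced by a two-sided t test at 5% and 80% power: the pooled SD is √((1.5² + 0.5²)/2) = 1.118, which needs 21 per arm. That is a separate matter and does not affect this point. On the stated SDs, 40 per arm gives about 98% power. If the rule removed a further 10% or 20% (assumed), 36 or 32 per arm would give about 96% or 94%. Power is not the main harm.

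**The case against.** The strongest reply is that the two sections govern different things: one says who stays in the study, the other how data are analysed. A patient withdrawn for drug use could be one of the dropouts that the analysis takes into consideration, kept in the assigned arm with data up to withdrawal, and GEE on repeated measures can use partial follow-up. This stands as a possible reading, so a reader who infers that the two statements cannot both hold goes too far. It does not remove the problem. The article does not state that reading, and under it CRP sampling still stops for a reason connected with CRP. Unweighted GEE is in general safe only when dropout does not depend on the outcome given the covariates.

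Other parts of the reply also stand:

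- Controls are not untreated; they receive supragingival scaling and hygiene instruction. That either treatment prompts these drugs is inference, not something the article says.
- In the 10% / 20% example the bias runs against the test treatment and is less than half a standard error.
- A reader might infer that these losses add to the 20% attrition. The Sample size section does not say what that figure covers, so it may include them.
- A reader might infer that the rule empties the trial of acetylsalicylic acid users. That depends on classing the drug as anti-inflammatory, which the article does not do, and on a share of users it does not give. The authors probably did not intend it, since they describe the drug as part of usual care in the clinic that supplies their patients.

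**Conclusion.** The concern holds in this form: as written, the follow-up exclusion conflicts with intention-to-treat, and on the most lenient reading it still produces, by design, missing CRP data related to the outcome and possibly to arm. This follows from the text and needs no assumed rate.

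The size and direction of the bias are not derivable. With 20% against 10% removed and reductions 1 mg/l smaller in those removed, the shift is about 0.1 mg/l, or 10% of the planned difference, in either direction depending on which arm loses more. If removal is equally frequent and equally selective in both arms, it is about zero.

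On acetylsalicylic acid the documents support only this: the exclusion rule and the Cardiovascular care section must be reconciled on whether the drug class includes it. The number of patients affected cannot be stated.

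**What to change.** 1. Replace the sentence so that no randomised patient leaves follow-up or the primary analysis because of drug use.
2. Record the type and dates of antibiotic and anti-inflammatory use at the same assessment visits (IV to VII) in both arms, with the same questions.
3. Use that information only in a pre-specified sensitivity analysis, for example setting aside CRP samples taken within a fixed window of an acute course.
4. If an entry criterion was meant, say so and apply it before randomisation.
5. Define the drug class and reconcile it with the acetylsalicylic acid use described under Cardiovascular care. Which way this is settled is for the investigators.

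The cost is a short amendment, a few questions at existing visits and one extra analysis. The downside is that some CRP values in the primary analysis will be noisier because samples near acute courses stay in. The Trial status section reports only a first block under treatment, so the change can still take effect for most patients.

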### Ethical considerations

All participants will read and sign an informed consent before entering the study. The study protocol was approved by the Institutional Review Boards of the university hospital (protocol no. 12–265) and the Federal University of Rio Grande do Sul (protocol no. 18341). The study will be conducted according to the principles of the Declaration of Helsinki for human studies and to the Brazilian legislation for human studies of the Ministry of Health.

### Cardiovascular care

This study will be conducted with stable coronary artery disease patients who will be receiving cardiovascular care for at least 6 months at the Ischemic Heart Disease Clinic, a tertiary care cardiovascular clinic, at the University Hospital of Porto Alegre. Cardiovascular care provided in this tertiary clinic includes medication and counseling. The staff of the clinic comprises cardiologists, nurses, nutritionists and physiotherapists. The protocol of cardiovascular care in this clinic includes statins for the majority of the patients. When appropriate, oral hypoglycemic, insulin, acetylsalicylic acid and antihypertensive drugs are also prescribed. Counseling includes mainly health-related lifestyle behavioral modifications such as daily exercise, smoking cessation and dietary therapy. The mean follow-up time of the patients that attend the clinic is 5 years.

### Sample size

The sample size of the present trial was estimated using a statistical software (G*Power 3 for Macintosh). The change in serum levels of C-reactive protein was considered the main outcome for sample size estimation. It was estimated that 42 individuals in each treatment arm will be necessary to find reductions in C-reactive protein of 1.5 mg/l (standard deviation = 1.5) and 0.5 mg/l (standard deviation = 0.5) in the test and control groups, respectively. Alpha and beta errors of 5% and 20%, respectively, were used in the estimation. An attrition rate of 20% is expected during the study; consequently, 50 patients in each group will be included.

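### The printed sample-size inputs need 21 patients per arm (42 in total), not 42 per arm; at 42 per arm the power is about 98%, not 80%

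*Protocol article*

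**What the plan says.** The Sample size section bases the calculation on the change in serum C-reactive protein (CRP), which is also the primary outcome, and names G*Power 3 as the software. The assumed reductions are "1.5 mg/l (standard deviation = 1.5) and 0.5 mg/l (standard deviation = 0.5) in the test and control groups, respectively". The error rates are given as "Alpha and beta errors of 5% and 20%, respectively, were used in the estimation". The result reads: "It was estimated that 42 individuals in each treatment arm will be necessary to find reductions in C-reactive protein of 1.5 mg/l" in the test arm. Attrition is handled afterwards: "An attrition rate of 20% is expected during the study", and so "50 patients in each group will be included". The section does not state the test family, the sidedness or any other allowance. The Statistical analyses section names the matching two-group comparison: "Univariate analyses will be conducted using chi-square and *t* tests for independent samples", followed by generalized estimating equations for the adjusted models.

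**The concern.** The section prints every quantity that a two-sample comparison of means needs, so its result can be checked directly, and it comes out at half the stated per-arm number. Nothing is missing here; the printed inputs and the printed output disagree.

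This paragraph is the only justification given for the size of the trial. A reader who accepts it will take a null CRP result as coming from a trial with 80% power for a 1.0 mg/l difference. If the printed means and SDs are right, the trial is far more sensitive than that, and a null result would be stronger evidence against a 1.0 mg/l difference than the text suggests. If the 42 is right, at least one printed input is not, and the published assumptions misdescribe the design. The attrition step starts from the same 42.

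**Working it through.** **Inputs (Sample size section).** Mean reductions 1.5 and 0.5 mg/l; SDs 1.5 and 0.5; alpha 0.05; power 0.80; equal arms. Two-sided testing is assumed because sidedness is not stated; one-sided is also shown.

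**Step 1: standardised effect.**
- Difference: 1.5 − 0.5 = 1.0 mg/l.
- Root-mean-square SD: √((1.5² + 0.5²)/2) = √((2.25 + 0.25)/2) = √1.25 = 1.118.
- d = 1.0/1.118 = 0.894, so d² = 0.80.

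**Step 2: attempt to reproduce 42 per arm.** The normal approximation is n per arm = 2(z₀.₉₇₅ + z₀.₈₀)²/d² = 2(1.960 + 0.842)²/0.80 = 2 × 7.849/0.80 = 19.6, so 20 per arm. The exact noncentral t calculation gives 20.63, so **21 per arm and 42 in total** (power 80.7% at 21). The stated figure is not reproduced as a per-arm number.

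**Step 3: other choices that keep the printed means and SDs.**

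| Choice | n per arm |
|---|---|
| Two-sided t, 80% power | 21 |
| Unequal-variance (Welch) t, two-sided, 80% | 22 (79.5% power at 21, 81.4% at 22) |
| One-sided t, 80% | 17 |
| Wilcoxon-Mann-Whitney, two-sided, 80% (relative efficiency 0.955 / 0.864) | 22 / 24 |
| Two-sided t, 90% power | 28 |
| Two-sided t, 95% power | 34 |

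None is close to 42.

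**Step 4: choices that replace a printed input.**

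| Replacement | n per arm |
|---|---|
| Common SD 1.5, two-sided t, 80% | 37 |
| Common SD 1.5, rank test at minimum efficiency 0.864, two-sided, 80% | 43 |
| Common SD 1.5, rank test at efficiency 0.955, one-sided, 90% | 42 |
| Variance not halved, SD = √2.5 = 1.58, two-sided, 80% (normal / t / rank test at 0.955) | 40 / 41 / 43 |

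For an unadjusted two-sided t test at 80% power and a 1.0 mg/l difference, 42 per arm detects d = 0.619, which corresponds to a common SD of 1/0.619 = 1.62. The protocol does not state that SD.

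**Step 5: power on the printed inputs.** The noncentrality is d√(n/2), with 2n − 2 degrees of freedom.

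| n per arm | Noncentrality | Power, t test | Power, Welch |
|---|---|---|---|
| 21 | 0.894 × √10.5 = 2.90 | 80.7% | 79.5% |
| 40 (50 less 20%) | 0.894 × √20 = 4.00 | 97.7% | 97.5% |
| 42 | 0.894 × √21 = 4.10 | 98.2% | 98.0% |
| 50 | 0.894 × √25 = 4.47 | 99.3% | 99.3% |

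At 42 per arm beta is therefore 1.8%, not 20%.

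**Step 6: difference detectable with 80% power.** At 42 per arm, 0.619 × 1.118 = 0.69 mg/l. At 40 per arm, 0.634 × 1.118 = 0.71 mg/l.

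**The case against.** The strongest reply is that the error is conservative. On the printed inputs the trial is larger than it needs to be, exceeds its target power even with 40 completers per arm, and requires no change in enrolment. That is correct, and it limits the harm to how the design is described and how a null result is read. It does not make the stated number or the stated beta true.

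The second reply concerns cause. The match between the t-test total of 42 and the published per-arm 42 suggests a total read as a per-arm figure, but this is inference. Step 4 shows that an un-halved variance, or a common SD of 1.5 with a rank test, also lands near 42, and the Statistical analyses section does foresee skewed data. Those routes contradict the printed inputs, so they do not rescue the paragraph, but they mean the misprint could lie in an input. The true power would then be much lower: at 40 per arm it is 83.8% with a common SD of 1.5 (t test), and just under 80% with SD 1.58, for which 41 per arm are needed. This part of the objection stands, and it governs the order of the correction: no new power figure should be published until the original inputs are known.

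A third possibility is an unstated allowance. The section applies attrition separately, after the 42, and names no other inflation.

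**Conclusion.** The point holds. With a 1.0 mg/l difference, SDs of 1.5 and 0.5, 5% two-sided alpha and 80% power, the requirement is 21 per arm (22 with an unequal-variance test). The stated 42 per arm is twice the t-test figure and equals its total. At that size the printed inputs give about 98% power, so the claim of 20% beta at 42 per arm is false. No standard test, sidedness or power level tried with the printed means and SDs returns 42 per arm. The 98% figure depends on those printed means and SDs being the intended ones; the mismatch itself does not. The cause is not established by the text.

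**What to change.** First retrieve the original G*Power record: test family, sidedness, means, SDs, and whether 42 was the total or the per-arm output. Then correct the item that is wrong.

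- If the printed means and SDs are right, keep 50 per arm and restate the justification along these lines: *The assumptions require 21 patients per arm (42 in total; 22 per arm with an unequal-variance t test) for 80% power at a two-sided 5% level. With 50 randomised and 40 completing per arm, power is about 98% for a difference of 1.0 mg/l, or 80% for a difference of 0.71 mg/l.*
- If 42 per arm came from other inputs, print those inputs with the test and sidedness, and give the power at 40 completers per arm on that basis.

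Either way the cost is a text correction, and the enrolment target does not change.

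### On the Sample size section's own figures, 50 per arm with 20% attrition leaves 40, two fewer than the 42 it calls necessary; the text needs restating, but the trial is not shown to be underpowered

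*Protocol article*

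**What the plan says.** The Sample size section of the protocol article takes the change in C-reactive protein (CRP) as the outcome for the calculation and makes these statements:

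- Requirement: "It was estimated that 42 individuals in each treatment arm will be necessary".
- Inputs: "reductions in C-reactive protein of 1.5 mg/l (standard deviation = 1.5) and 0.5 mg/l (standard deviation = 0.5) in the test and control groups".
- Error rates: "Alpha and beta errors of 5% and 20%, respectively, were used in the estimation". Whether the test is one- or two-sided is not stated.
- Attrition and enrolment: "An attrition rate of 20% is expected during the study; consequently, 50 patients in each group will be included".

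The Methods/design part of the Abstract agrees on the total: "One hundred individuals will be allocated to test" or control. So 50 per arm is not a misprint. No other attrition allowance appears, and no other reason for choosing 50.

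**The concern.** The section presents 50 per arm as the consequence of a 42-per-arm requirement and 20% expected loss. Attrition acts on those enrolled, so the number enrolled has to be the requirement divided by the proportion retained. Fifty is too small for that. As written, the trial could lose exactly the share of patients it expects to lose and still finish below the minimum it has set for itself.

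The sample-size statement is the yardstick against which retention on the primary outcome will be judged, and here the yardstick disagrees with itself. A reader who took 42 at face value could also draw a wrong conclusion about power.

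**Working it through.** **Inputs, all from the Sample size section.** Requirement 42 per arm; expected attrition 20%; enrolment 50 per arm; mean CRP reductions 1.5 and 0.5 mg/l with SDs 1.5 and 0.5; alpha 5%; power 80%. A two-sided test is assumed.

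**Step 1: where 50 might come from.** Multiplying the requirement by one plus the attrition rate gives 42 × 1.20 = 50.4, which rounds down to 50. The section does not say how 50 was reached, so this is an inference that fits the figure.

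**Step 2: the attrition allowance.**

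- Completers from 50 per arm: 50 × (1 − 0.20) = 40, which is 2 below 42.
- Enrolment needed to keep 42: 42 / (1 − 0.20) = 52.5, so 53 per arm (106 in total).
- Largest loss that 50 per arm can absorb and still leave 42: 1 − 42/50 = 16%.

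Rounding does not explain the gap: 52.5 cannot round to 50, and even 50.4 would be rounded up to 51 to protect a minimum.

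**Step 3: does 42 per arm follow from the printed inputs?**

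- Difference: 1.5 − 0.5 = 1.0 mg/l.
- Root-mean-square SD: √[(1.5² + 0.5²)/2] = √1.25 = 1.118 mg/l.
- Standardised difference: 1.0/1.118 = 0.894.

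Number per arm for 80% power at 5%, under several readings:

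| Reading | n per arm |
|---|---|
| Two-sided, SD 1.118, normal approximation | 20 |
| Two-sided, SD 1.118, t test | 21 |
| Two-sided, unequal-variance (Welch) t test | 22 |
| One-sided, SD 1.118 | 16 to 17 |
| Two-sided, SD 1.5 in both arms | 36 to 37 |
| Two-sided, SD 1.0 in both arms | 16 to 17 |

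None gives 42 per arm. The two-sided t test gives 21 per arm, which is 42 in total. A total may have been reported as a per-arm figure, or the inputs may have been reported wrongly; the document does not settle which.

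**Step 4: power on the printed inputs (two-sided t test, SD 1.118).**

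| n per arm | Power |
|---|---|
| 21 | 80.7% |
| 40 | 97.7% |
| 42 | 98.2% |
| 50 | 99.3% |

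The Welch test gives 97.5% at 40 per arm. With SD 1.5 in both arms, 40 per arm still gives 83.8%.

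**Step 5: if 42 per arm were truly needed for 80% power.** The standardised difference would have to be 0.619, and 40 per arm would then give 78.0%. This value is back-solved and appears nowhere in the document. With a difference of 1.0 mg/l it implies a common SD of 1.0/0.619 ≈ 1.62 mg/l, larger than either printed SD.

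**The case against.** **The 42 is itself doubtful, so missing it may not matter.** This is the strongest objection, and it stands as to consequence. Against the printed inputs the need is about 21 per arm; 21/0.80 = 26.25, so 27 enrolled per arm would do, and 50 absorbs 20% attrition with a wide margin. It does not make the attrition sentence correct, because that sentence is built on 42. It does mean that the base figure must be settled at the same time.

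**Dropouts are not wholly lost.** The Statistical analyses section plans an intention-to-treat approach and generalized estimating equations, and CRP is measured at baseline, 3, 6 and 12 months. A patient who leaves after 3 or 6 months can still contribute CRP data, so the number analysed may exceed the number who complete. This reduces the practical effect further. It does not mend the sum: the Sample size section itself adds patients for attrition, takes no credit for partial follow-up, and the article states no method for recovering missing CRP values.

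**The article is condensed.** That would excuse something left out. Here all three figures are printed, and they disagree.

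**The tempting stronger reading.** A reader might infer that the trial is underpowered, or that it must enrol 106 patients. The document does not support either. The 78.0% in Step 5 depends on an effect size the plan never states, while the plan's own inputs give about 98% power at 40 per arm. The figure of 53 per arm matters only if 42 per arm can be justified from inputs other than those printed.

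**Conclusion.** The attrition sentence is wrong on its own figures: 50 per arm with 20% loss leaves 40, not 42. The shortfall is 2 completers, or 3 enrolled patients, per arm, and 50 per arm tolerates 16% attrition. That part rests on simple arithmetic and needs no assumption beyond treating lost patients as the section itself does.

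The practical weight is small. Assuming a two-sided 5% test and the printed means and SDs, 40 per arm gives about 98% power. The same check shows that 42 does not reproduce as a per-arm requirement (about 21 per arm, 42 in total). Correcting the attrition sentence alone would therefore leave the section inconsistent.

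**What to change.** Restate the Sample size section so that the requirement, inputs, attrition and enrolment agree. No additional enrolment is called for. First settle which base figure is meant:

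- **If 42 per arm is kept:** give the inputs that produce it, including whether the test is one- or two-sided, and state that 50 per arm allows for 16% attrition.
- **If the printed inputs are right:** correct the base requirement to about 21 per arm (42 in total), and state that 50 per arm with 20% attrition leaves 40 per arm and about 98% power.

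The two should not be mixed. Quoting about 98% power at 40 per arm next to an unchanged sentence requiring 42 per arm at a 20% beta error would create a new contradiction. The revised wording should also not tie the 40 to 12-month data, because the Primary outcome section does not fix a 12-month contrast.

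The cost is a text correction. If 42 is kept, the stated tolerance for attrition becomes slightly less favourable, at 16% instead of 20%.
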